### 2.13. Ethics and Dissemination

The trial has been approved by the Area-Vasta Emilia-Romagna Centro Ethics Committee with approval number 898/20. Written informed consent will be obtained from all participants. Upon conclusion of the trial, the research coordinator will be responsible for the final dataset that will be published in a public repository and made accessible to researchers.

The results of the present study will be published in peer-reviewed journals and presented at national and international congresses. Moreover, the trial reports and publications will be made available to local stakeholders and policymakers and shared within patients’ associations.

### 2.14. Patient and Public Involvement

The study protocol, including intervention and outcome measures, was conceived without patients or public involvement. However, patients will be considered as a route to disseminate the research findings by word of mouth to other patients, especially within patients’ associations. General practitioners will also be involved in the dissemination of the study results, especially among their patients.

## 3. Conclusions

In conclusion, this study may fill in a piece of missing information regarding exercise trials in PAD patients with claudication, addressing some research priorities for exercise interventions recently reported by experts [5]. Leading scientists are indeed advocating studies concerning tailored therapy for different patient abilities; comparing exercise training modalities to maximize adherence and participation; and identifying optimal strategies to transfer patients from supervised, hospital-based settings to community-based settings. Given that a recent trial highlighted the non-superior effect of low-intensity exercise interventions compared to controls in terms of walking ability over 12 months [19], we believe that a different, structured pain-free model of home-based exercise may positively impact the functional capacity and quality of life of claudication patients. In the event of positive results, this program may also be extended to fragile patients with a reduced exercise capacity or with a high degree of PAD severity. The validation of a sustainable and effective patient-centered exercise program compared to usual care may represent a strategic issue for the Health Service to reduce revascularizations, physical decline and hospitalizations in patients with PAD as well as in elderly or frail individuals.

## Figures and Tables

**Table 1 mps-04-00029-t001:** Weekly training progression for patients randomized into TiTo-SHB group.

Week	Walk:Rest Ratio (min)	Repetitions	Speed Steps/min–km/h
1	1:1	8	60–1.5
2	1:1	8	60–1.5
3	1:1	8	63–1.7
4	1:1	8	63–1.7
5	1:1	8	66–1.9
6	1:1	8	66–1.9
7	1:1	8	69–2.2
8	1:1	8	72–2.4
9	1:1	8	72–2.4
10	1:1	8	76–2.7
11	1:1	8	76–2.7
12	1:1	8	80–3.0
13	1:1	8	76–2.7
14	1:1	8	80–3.0
15	1:1	8	84–3.2
16	1:1	8	84–3.2
17	1:1	8	88–3.5
18	1:1	8	88–3.5
19	1:1	8	92–3.8
20	1:1	8	84–3.2
21	1:1	8	88–3.5
22	1:1	8	92–3.8
23	1:1	8	96–4.0
24	1:1	8	100–4.2

**Table 2 mps-04-00029-t002:** Outcome measures flow diagram. The line represents the duration of the treatments.

	Study Period			
	Enrollment	Allocation	Post-Allocation	Close-Out
Time point	−15 days (maximum)	0 Baseline	6-month end of training	12-month
Eligibility screening	X			
Informed consent	X			
Allocation		X		
Randomization		X		
Interventions				
Structured Home Based Exercise				
Control (walking advice)		X	X	
Outcomes				
Pain-free walking distance [primary outcome]		X	X	
6-min walking distance, lower limbs strength, quality of life, foot temperature [secondary]		X	X	
Hospitalizations and mortality			X	X

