## Abstract

Exercise therapy in the intermediate stages of peripheral artery disease (PAD) represents an effective solution to improve mobility and quality of life (QoL). Home-based programs, although less effective than supervised programs, have been found to be successful when conducted at high intensity by walking near maximal pain. In this randomized trial, we aim to compare a low-intensity, pain-free structured home-based exercise (SHB) program to an active control group that will be advised to walk according to guidelines. Sixty PAD patients aged > 60 years with claudication will be randomized with a 1:1 ratio to SHB or Control. Patients in the training group will be prescribed an interval walking program at controlled speed to be performed at home; the speed will be increased weekly. At baseline and after 6 months, the following outcomes will be collected: pain-free walking distance and 6-min walking distance (primary outcome), ankle-brachial index, QoL by the VascuQoL-6 questionnaire, foot temperature by thermal camera, 5-time sit-to-stand test, and long-term clinical outcomes including revascularization rate and mortality. The home-based pain-free exercise program may represent a sustainable and cost effective option for patients and health services. The trial has been approved by the CE-AVEC Ethics Committee (898/20). Registration details: Clinicaltrials.gov NCT04751890 [Registered: 12 February 2021].

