### 2.7. Outcomes

The outcome measures will be performed at study entry prior to randomization (T0), at the end of the training program (6 months, T1) and after the 12-month follow-up (T2).

The primary outcome measure will be the 6-min walking test [35]. Patients will be asked to walk back and forth in a standard 20-m corridor with the goal of covering as much distance as possible in 6 min. Patients will be asked to report the distance at which claudication symptoms began, which will be recorded as pain-free walking distance (PFWD). When necessary, they will be allowed to stop as needed and restart whenever possible. The total distance walked, or 6-min walking distance (6MWD), will be measured. Heart rate will be continuously measured throughout the test with a heart rate monitor, and maximal oxygen consumption may be calculated according to the published formulas. The rate of perceived exertion (RPE), according to the 1-10 Borg RPE scale, will be collected at the end of the test [36]. The minimal clinically important difference for 6MWD will be set at 36 m [37].

Secondary outcomes will include the following:

The ABI will be measured according to published standards [38]. With the patients lying in a supine position, blood pressure values at the posterior tibial and dorsalis pedis arteries will be collected, along with systolic blood pressure. The ratio of the highest value measured in each leg to the pressure measured in the arm will be used to obtain the ABI values.

The Vascular Quality of Life Questionnaire-6 (VascuQoL-6) is composed of 6 questions that assess the impact of PAD on patients’ quality of life in the previous two weeks. The scores range from 6 to 24, where a higher score corresponds to a better QoL [39].

Foot temperature will be measured with an infrared thermal camera (FlirOne Pro, Flir, Milan, Italy) at three points on the dorsum of each foot: the posterior tibial artery behind the malleolus, the anterior tibial artery at the ankle, and the dorsalis pedis artery on the dorsum of the foot.

A five-time sit-to-stand test will be used to measure lower limb strength. The patient will sit with both arms folded across his/her chest, and he/she will be asked to stand and sit five times consecutively, aiming to complete them as quickly as possible. The total elapsed time will be recorded.

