### 2.8. Sample Size Calculation

Based on published data we observed the variations in 6MWD in TiTo-SHB program and in other trials including groups at usual care [20,23]. Considering a baseline mean 6MWD of 300 m, with 27 patients for each group, the study will have 90% power to confirm the superiority of TiTo-SHB respect to walking advice, with a superiority margin set at the minimal clinically important difference or 36 m [37]. Allowing for a possible 10% dropout rate during the trial, a sample size of 60 patients (30 per group) will be planned.

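### Table 2 makes pain-free walking distance the primary outcome and 6-min walking distance secondary, but the trial is sized on 6-min walking distance

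*Protocol article*

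**What the plan says.** Five places in the protocol article bear on which variable is primary.

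- **Table 2.** One row is labelled "Pain-free walking distance [primary outcome". The next is labelled "6-min walking distance, lower limbs strength, quality of life, foot temperature [secondary". PFWD is primary here and 6MWD is explicitly secondary.
- **Abstract.** The outcome list opens with "pain-free walking distance and 6-min walking distance (primary outcome". The tag is singular and follows two distances.
- **Section 2.7.** "The primary outcome measure will be the 6-min walking test", which is a test and not a variable. Two variables are taken from it: the distance at symptom onset, "which will be recorded as pain-free walking distance (PFWD", and then "The total distance walked, or 6-min walking distance (6MWD), will be measured". The minimal clinically important difference of 36 m is given for 6MWD, and none is given for PFWD. Neither distance appears in that section's list of secondary outcomes.
- **Section 2.8.** The sample size rests on 6MWD: "Considering a baseline mean 6MWD of 300 m, with 27 patients for each group", with 90% power and a superiority margin of 36 m.
- **Section 2.12.** Every outcome is compared between groups by the same choice of t-test or Mann-Whitney test, with significance at p < 0.05. No outcome is singled out as primary.

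**The concern.** A trial needs one identified variable, or a stated set with a rule, on which its main conclusion rests. Here the outcome table and the sample size section point to different variables. Two things follow.

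First, the power statement attaches to 6MWD. If Table 2 is followed, the primary analysis concerns a variable for which the document gives no expected value, effect, spread or important difference, so the 90% does not carry over.

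Second, with the label unsettled, a report could present either distance as the primary result and cite this article in support. Both would be tested at 0.05, so the chance of a false positive on at least one of them exceeds 5%.

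**Working it through.** **1. The statements side by side**

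| Place | PFWD | 6MWD |
|---|---|---|
| Table 2 | primary | secondary |
| Abstract | primary or untagged, depending on reading | primary |
| Section 2.7 | taken from the primary test | taken from the primary test, with a 36 m important difference |
| Section 2.8 | not mentioned | sized |

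No reading of the Abstract, 2.7 or 2.8 makes 6MWD secondary. Table 2 cannot be reconciled with them.

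**2. The plan's own figure**

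Inputs from Section 2.8: 27 per group, 10% dropout, 90% power, 36 m.

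Dropout step: 27 / (1 − 0.10) = 30 per group, 60 in total. This reproduces.

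The 27 itself cannot be reproduced, because the article states neither a standard deviation nor an expected difference. It can only be solved backwards. If 36 m is read as the difference to detect, n = 2(z₁₋α + z₀.₉₀)² SD² / 36², so SD = 36 / [(z₁₋α + z₀.₉₀) √(2/27)], with z₁₋α replaced by z₁₋α/₂ for a two-sided test:

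- two-sided 0.05: 36 / [(1.960 + 1.282) × 0.2722] = 36 / 0.882 ≈ 41 m (40 m by the exact t calculation)
- one-sided 0.05: 36 / [(1.645 + 1.282) × 0.2722] = 36 / 0.796 ≈ 45 m

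If 36 m is instead a true superiority margin, the true difference needed at two-sided 0.05 is 36 + 3.242 × SD × 0.2722. That is about 71 m for an assumed SD of 40 m and 89 m for an assumed SD of 60 m.

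All of these quantities concern 6MWD. No corresponding calculation can be set up for PFWD from the document.

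**3. Type I error if either distance could count**

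This is conditional on a rule that the article does not state. With each distance tested two-sided at 0.05 and ρ the correlation of the two test statistics (assumed, since the article gives none), the error is 1 − P(|Z₁| < 1.96, |Z₂| < 1.96) under a bivariate normal:

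| ρ | Chance that at least one is significant |
|---|---|
| 0 | 1 − 0.95² = 9.75% |
| 0.5 | 9.1% |
| 0.7 | 8.3% |
| 0.8 | 7.8% |
| 0.9 | 7.0% |

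Both distances come from the same walk, so independence is an upper reference and not a realistic case. Counting only results that favour the exercise arm, the nominal 2.5% becomes 4.5% at ρ = 0.5 and 3.5% at ρ = 0.9.

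**4. Cost of keeping both distances as alternatives**

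Take the standardised effect implied by 27 per group at two-sided 0.05, d = 36 / 40.8 ≈ 0.88, and assume that it applies to each distance. Splitting alpha to 0.025 each gives n = 2(2.241 + 1.282)² / 0.882² ≈ 32 per group, or 32 / 0.9 ≈ 36 per group after dropout. At 27 per group, power for one distance is Φ(0.882 / 0.2722 − 2.241) = Φ(1.00) ≈ 84%, down from 90%.

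**The case against.** The strongest reply is that Table 2 is a single mislabelled table. The Abstract's singular tag stands directly after 6MWD and may refer to it alone. Section 2.7 is compatible with that reading, gives an important difference for 6MWD only, and leaves both distances off its secondary list. Section 2.8 sizes 6MWD. On this view the intended primary is clear enough, and any multiplicity rule may stand in an analysis plan that is not shown.

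Much of this stands. A reader might infer that the article defines the primary outcome in three incompatible ways. It does not: the Abstract and Section 2.7 are ambiguous but compatible with each other, and the outright contradiction lies between Table 2 and the rest. A reader might also infer that the trial is set up to succeed on whichever distance is significant. No such success rule appears anywhere, and the absence of an alpha allocation in a condensed article is not an error in itself.

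Two further inferences are not supported. One is that patients who finish the test without pain would have PFWD multiply imputed. Section 2.12 says only that missing values are imputed and does not say that such patients have a missing value. The other is that PFWD would be biased by a particular amount. The article gives no mean, spread or correlation for it.

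What does not stand is the suggestion that the intended primary is plain. Table 2 states the opposite in intact words for both rows, and neither the Abstract nor Section 2.7 names 6MWD alone. A separate analysis plan could choose one variable, but this document would still contradict itself.

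**Conclusion.** The point holds as an internal contradiction over the primary variable: Table 2 against Section 2.8 and against the important difference in Section 2.7, with the Abstract and the naming of the test in 2.7 leaving it unresolved. It should be corrected before any analysis, because it decides which comparison the trial's conclusion rests on.

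The part that needs no assumption is that, if Table 2 is right, the 90% power has no basis in the document. The type I error of about 7.0% to 9.1% (9.75% if independent) is a conditional figure. It rests on assumed correlations of 0.9 to 0.5, two-sided testing at 0.05, and an either-or claim that the article neither states nor excludes.

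**What to change.** Name one primary endpoint: the between-group difference in 6MWD at 6 months (T1), which is the distance that was sized. Then align the text:

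- **Table 2:** move the primary label to 6MWD and list PFWD as secondary.
- **Section 2.7:** name 6MWD at T1, not the test, as the primary outcome, and add PFWD to the secondary outcomes.
- **Abstract:** attach the primary tag to 6MWD alone.

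This is a change of wording only, with no added patients, visits or procedures. Its price is that PFWD, the distance closest to the pain-free idea of the programme, can no longer carry the primary claim.

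If the investigators want both distances to count, they can say so with an explicit alpha rule and a re-derived sample size. On the assumptions above, an equal split needs about 36 per group (72 in total) in place of 30 (60 in total), and PFWD would need its own stated effect and spread.

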## Data Availability

Not applicable.
